#### Safety

Adverse events will be assessed through the frequency and severity of adverse events reported during remotely monitored exercise sessions, any unsupervised exercise sessions, and exercise testing sessions (as outlined in the “Cardiovascular Fitness: VO_2_peak” section). Severity will be graded according to the Common Terminology Criteria for Adverse Events 5.0 and the National Health and Medical Research Council guidelines for safety monitoring and reporting [32,40]. Participants will be instructed to immediately report any adverse events that occur during the intervention period (during either supervised or unsupervised exercise sessions) to the study staff (ie, exercise professionals or study coordinators); these will be recorded. All adverse events reported to study staff will be communicated to the study coordinator and the coordinating principal investigator as soon as possible and recorded. The coordinating principal investigator will be responsible for ensuring serious adverse events are reported to the ethics committee and trial sponsor within the appropriate time frames. Participants can also retrospectively report adverse events during the postintervention and follow-up surveys. The trial will be deemed safe if no grade ≥3 adverse events attributed to participating in the research project are reported. During the intervention period, participants can also self-report symptoms (new, ongoing, or worsening) through the smartphone app at the beginning and end of every exercise session (supervised and unsupervised). Any changes in symptomology will also be recorded.

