### Trial Design

A single-arm feasibility study will be conducted to determine the feasibility, safety, and preliminary efficacy of REMOTE-COR-B (protocol version 7; date August 24, 2023). The trial has been prospectively registered on the Australian New Zealand Clinical Trials Registry (ACTRN12621001557820). The study protocol is reported in accordance with the SPIRIT (Standard Protocol Items: Recommendations for Interventional Trials) guidelines [20], and the intervention is described according to the Consensus on Exercise Reporting Template (CERT) [21]. Study materials are available on the Open Science Framework [22].

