### Outcomes and Assessment Timing

Data relating to intervention delivery outcomes (eg, adherence, feasibility, and safety) will be collected during the 8-week intervention (Table 1). Satisfaction and usability will be assessed post intervention. Objective and patient-reported efficacy outcomes will be assessed at baseline (within 24 months post completion of primary definition treatment), post intervention (2-month postbaseline assessment), and at follow-up (5-month postbaseline assessment). Demographic and medical data will be collected at baseline through self-reports and medical records. Criteria of success for core feasibility, usability, safety, and efficacy outcomes have been prespecified and are outlined below.

**Table 1 table1:** Schedule of enrollment, intervention, and assessments for REMOTE-COR-B: a single-arm feasibility trial for patients with breast cancer (based on the SPIRIT [Standard Protocol Items: Recommendations for Interventional Trials] guidelines) [20].

Time point		Study period					
		Enrollment (prebaseline)	Intervention period				Follow-up
			Baseline (0 months)	Intervention (2 months)	Postintervention (2-month postbaseline)	Follow-up (5-month postbaseline)	

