### Secondary Outcomes

#### Trial Feasibility

Trial feasibility is assessed based on rates of screening, consent, device ownership, retention, and missing data across all assessment points. Prespecified cut points indicating feasibility include cardiac dysfunction risk level is accessible for ≥80% of cases identified; ≥60% of those invited to participate agree to complete eligibility screening [39]; the recruitment goal is reached within the allotted time (1 year); retention is ≥60%; and outcome data are collected for ≥80% of enrolled participants at both the postintervention and follow-up assessments (this is in line with retention observed by the chief investigator [name] et al [19] in the REMOTE-CR trial).

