### Data Analysis

#### Sample Size

We aim to recruit 40 participants over the course of 12 months. This sample size is considered sufficient to test the feasibility of delivering the intervention and other key trial parameters [62]. Notably, with this sample size, we will also have reasonable precision for estimating intervention adherence. For example, with a sample size of 40, if the average adherence rate observed in the study is 70%, we can be sure with 95% confidence that the true population proportion is between 56% and 85%; the 95% CI is ≥14.2. Given the potential reach of the intervention and the fact that adherence to current technology-based behavior change programs is 50% [39], this finding would warrant further investigation. The target sample size is also equivalent to approximately 20%-30% of the sample size needed to adequately power (80%) a future definitive trial to demonstrate noninferiority in VO_2_peak changes between groups (a *P* value of .05); based on differences observed in our formative work [19] and a systematic review [8].

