#### Statistical Methods

The data will be presented descriptively where appropriate; this includes most feasibility outcomes (eg, recruitment rate, proportion of missing data, usability, and satisfaction), including the primary outcome (ie, adherence to the intervention), and safety outcomes (eg, number of adverse events, proportion of serious adverse events).

Changes in VO_2_peak, patient-reported outcomes (quality of life and fatigue), and physical activity behavior will be examined in exploratory analyses at all assessment time points using mixed model repeated measures analyses. Unadjusted and age- and treatment pathway–adjusted models will be conducted with standardized coefficients reported with 95% CIs to aid interpretation of clinical significance rather than *P* values given a lack of statistical power. The choice of modeling link will be informed by residual diagnostics. The data for withdrawn participants collected before study withdrawal will be retained for use in intention-to-treat analyses, unless requested otherwise by the participant.

Further exploratory analyses may include (1) examining changes in the proposed psychological mechanisms (eg, self-efficacy) from baseline to postintervention; (2) examining associations between the proposed mechanisms and the study outcomes (eg, adherence to exercise sessions and cardiorespiratory fitness); and (3) examining associations between participant characteristics (potential moderators) and intervention adherence (sessions and intensity), as well as changes in VO_2_peak. Given the small sample size and absence of a control group, a formal mediation analysis or moderation analysis will not be undertaken (as per Baron and Kenny [63]). However, the collection of these data will assist with determining the feasibility of mediator and moderator assessment in a larger trial, where a formal mediation analysis and moderator analysis may be undertaken.

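### Zero attributable grade ≥3 events among 40 single-arm participants cannot support a verdict of 'safe', and event collection is worded around exercise sessions with an inconsistent time window

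*Protocol article*

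**What the plan says.** **The rule.** Under Secondary Outcomes, Safety: "The trial will be deemed safe if no grade ≥3 adverse events attributed to participating in the research project are reported". Outcomes and Assessment Timing presents this and the other cut points as prespecified criteria of success.

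**The design.** Trial Design: "A single-arm feasibility study will be conducted". Sample Size: "We aim to recruit 40 participants over the course of 12 months". The only precision statement there concerns adherence: with 70% observed, the "true population proportion is between 56% and 85%; the 95% CI is ≥14.2". Statistical Methods treats "safety outcomes (eg, number of adverse events, proportion of serious adverse events") descriptively. No tolerable event rate or confidence limit is attached to the safety verdict.

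**What is collected.** The Safety section assesses events reported during monitored sessions, unsupervised sessions and exercise tests. Participants are told to report at once "any adverse events that occur during the intervention period (during either supervised or unsupervised exercise sessions"). The same section lets them report adverse events afterwards in the postintervention and follow-up surveys, and lets them enter symptoms in the app at the start and end of each session. The section on adaptations for breast cancer adds a symptom prompt at the start of each session.

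**When.** Outcomes and Assessment Timing: "Data relating to intervention delivery outcomes (eg, adherence, feasibility, and safety) will be collected during the 8-week intervention". The Methods paragraph of the Abstract says the same. Table 1 ticks safety at baseline, during the intervention, post intervention and at follow-up.

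**The concern.** A count of zero in a small sample is weak evidence about a rate, yet the rule turns it into an unqualified conclusion. The article's own Abstract describes these patients as having heightened safety risks and says the project's information on safety is needed before larger research or clinical projects. The Discussion adds that the findings might inform implementation in breast cancer services. A verdict of 'safe' would therefore travel further than a descriptive feasibility result normally does.

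The verdict also turns on events being reported. If the wording steers prompt reporting towards what happens during a session, a delayed event related to exercise is more easily missed, and a missed event counts in favour of safety. If the collection window is unclear, so is whether a severe event at the baseline or 5-month exercise test counts against the rule.

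**Working it through.** **Inputs.** Planned n = 40 (Sample Size). Single arm (Trial Design). Rule: pass if zero attributable grade ≥3 events (Safety). The tolerable or true rate is not given, so 1% to 5% of participants is assumed below. Participants are treated as independent with a common event probability p, and all 40 as observed.

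**The plan's own precision figure.** For adherence, the normal-approximation half-width is 1.96 × √(0.70 × 0.30 / 40) = 0.142, giving 55.8% to 84.2%. The 14.2 points and the lower limit of 56% are reproduced; the upper limit rounds to 84%, where the article has 85%. So the plan does attach a 95% interval to a proportion from 40 people, but for adherence only.

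**What zero events in 40 excludes.** The upper limit solves (1 − p)^40 = α.

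- One-sided 95%: 1 − 0.05^(1/40) = 0.072, or 7.2%.
- Two-sided exact 95%: 1 − 0.025^(1/40) = 0.088, or 8.8%.

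A true rate of 8.8% is about 1 participant in 11 (1/0.088 = 11.4).

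**How often the rule returns 'safe'.** The probability is (1 − p)^40.

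| Assumed true rate | Probability of 'safe' |
|---|---|
| 1% | 0.99^40 = 67% |
| 2% | 0.98^40 = 45% |
| 3% | 0.97^40 = 30% |
| 5% | 0.95^40 = 13% |

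The rule is fragile in the other direction too: at a true rate of 1% it fails with probability 1 − 0.669 = 33%, and one event is enough.

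**Scale of the shortfall.** With zero events, a one-sided 95% upper limit of at most u needs n ≥ ln(0.05)/ln(1 − u). That is 59 participants for u = 5%, 99 for 3% and 149 for 2%. This shows what 40 cannot deliver; it is not a proposal to enlarge the trial.

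**Capture, side by side.**

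- Assessment sentence: events during monitored, unsupervised or testing sessions.
- Immediate-reporting instruction: intervention period, limited in brackets to exercise sessions.
- App symptom reports and start-of-session prompts: can pick up a problem that arose between sessions, provided the participant starts another session.
- Two surveys: no session limit, but optional and retrospective, at 2 and 5 months.

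The first two routes, read literally, leave out an event that begins hours after exercise. The last two can catch it, with delay and without certainty.

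**Window, side by side.** The Abstract and Outcomes and Assessment Timing place safety collection in the 8 weeks. Table 1 adds baseline, post intervention and follow-up. The Safety section counts exercise tests, and Table 1 schedules CPET and ISWT at baseline, 2 months and 5 months, so the baseline and 5-month tests lie outside the 8 weeks.

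**The case against.** The strongest reply is that this is a feasibility study. Safety is descriptive, the efficacy aim is preliminary, no population rate is claimed, and a later powered trial is foreseen. An exact interval around a safety proportion is ordinary analysis-plan content, and that plan is not shown. The rule is also strict in one sense: at a true rate of 5% it fails 87% of the time, and without a stated tolerable rate nobody can call a pass at 1% or 2% an error. Much of this stands. The absence of an interval is not itself the fault, and the 1% to 5% range is an assumption. What does not fall away is the label: the article itself fixes a conclusion of safety that its sample size cannot carry.

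On capture, the reply is that routes not bound to sessions exist, and that with three monitored sessions a week an attending participant is prompted again within days. That is correct. A reader might infer that between-session events are left entirely to later recall; the start-of-session prompts contradict this. A reader might also infer that participants who withdraw never complete the surveys; the article does not say so.

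A reader might further take the feasibility cut point, "retention is ≥60"%, and recompute the limits on 24 participants. The documents do not support that denominator. Statistical Methods keeps data collected before withdrawal unless the participant asks otherwise, and people who leave contribute exposure and events until they leave.

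On the window, the sentence about the 8 weeks cites Table 1 and does not say 'only'. The mismatch is real but small.

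**Conclusion.** The point holds. If the plan is followed as written, zero events in 40 yields a statement of safety while true attributable grade ≥3 rates of up to 7.2% (one-sided) or 8.8% (two-sided exact) remain compatible with the data. Over the assumed 1% to 5%, the chance of that statement runs from 67% to 13%. These figures rest on all 40 being enrolled and observed, and on complete reporting; fewer participants or missed events would weaken the conclusion further. Whether any rate in the range is acceptable is a clinical judgement the article does not make.

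The capture weakness is secondary and one of wording: the assessment sentence and the immediate-reporting bracket are narrower than the other routes in the same section. The window needs a short reconciliation. None of this affects the primary outcome, adherence.

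**What to change.** 1. In the Safety section, replace the verdict of safety with a statement that no safety signal was observed when there are no such events. Whatever the count, report the number and proportion of all enrolled participants with an attributable grade ≥3 event, with an exact 95% CI. State in advance that 0/40 leaves an upper limit of 8.8%.
2. Remove the session restriction from the assessment sentence and the immediate-reporting instruction, so that adverse events are recorded whenever they occur from the baseline exercise test to the 5-month assessment.
3. Reconcile the Abstract, Outcomes and Assessment Timing and the Safety section with Table 1, so that one collection window is stated and it is clear that events at the baseline and 5-month exercise tests count.

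The cost is a more modest safety statement and a slightly longer adverse-event log. No additional participants are needed.

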#### Satisfaction and Usability

Satisfaction with the intervention and perceived intervention usability will be assessed using the validated 8-item Client Satisfaction Questionnaire (0-32) [41] and the 10-item System Usability Scale (0-100) [42]. The intervention will be deemed satisfactory and usable if mean scores are ≥24 and ≥68, respectively. Issues with wearing the heart rate monitor due to cancer treatment-related discomfort will also be discussed and recorded by the study coordinator in a study-specific form.

#### Cardiovascular Fitness: VO2peak

Cardiovascular fitness (VO_2_peak) will be assessed through CPET and an incremental shuttle walk test (ISWT). The CPET will occur at the Peter MacCallum Cancer Centre (conducted by Peter MacCallum staff) and will involve participants exercising on an exercise bike against increasing resistance, during which time gas exchange analysis will be conducted to measure anaerobic threshold and VO_2_peak. Blood pressure and 12-lead ECG will be monitored for signs of an adverse cardiac response. VO_2_peak is a gold-standard measure for objectively assessing cardiorespiratory fitness and is an important clinical end point in this population because it is a strong predictor of adverse cardiovascular events and mortality [11]. A change in VO_2_peak as small as 6% can be clinically meaningful in terms of cardiovascular outcomes among patients with chronic systolic heart failure [43]. We expect an average improvement in VO_2_peak of ≥10%, as this is comparable to what has been achieved in posttreatment supervised exercise interventions among patients with breast cancer [44-46]. Additionally, this level of change is used clinically in a heart failure setting as indicating a clinically meaningful improvement in outcomes [47,48] and is associated with improved health-related quality of life in patients with breast cancer [46].

The ISWT is a valid and reliable field walking test to assess functional exercise capacity [49,50] and is shown to be moderately correlated with CPET-assessed VO_2_peak (*r*=0.61) [51]. Due to possible COVID-19–related difficulties with performing CPETs on all participants, an ISWT will also be performed (conducted by trial staff), as the equipment is easily transportable and the test can be completed outdoors (potentially necessary if a home visit is required due to COVID-19 restrictions and a suitable indoor location is not available). Participants are required to walk around 2 cones placed 9 meters apart (a total of 10 meters of flat course) in time to a set of auditory beeps. Initially, the walking speed is very slow, but each minute, the required walking speed progressively increases. The test concludes when the participant cannot achieve the required speed, experiences clinical indications for test termination, or wishes to stop. The number of shuttles is recorded. Only standardized instructions will be used [50], the walking track will be kept the same for all tests for a participant, and no encouragement will be given throughout. An improvement of ≥48 meters from baseline to postintervention will be considered clinically significant [49]. The intervention will be deemed potentially efficacious for improving cardiovascular fitness if clinically significant changes in VO_2_peak (≥10%) or meters walked in the ISWT are achieved.

#### Quality of Life

Quality of life will be assessed using the validated 38-item Functional Assessment of Cancer Therapy-Breast (FACT-B) questionnaire [52]. Total health-related quality of life (0-148) and subscale scores (physical, social, emotional, and functional well-being) will be calculated. A clinically important change in total quality of life has been defined as a 6% increase between baseline and postintervention [53].

#### Fatigue

Fatigue will be assessed using the validated 13-item Functional Assessment of Chronic Illness Therapy-Fatigue Scale (FACIT-Fatigue) questionnaire [54]. All items are summed to create a single fatigue score (0-52). A clinically important change in the FACIT-Fatigue has been defined as a 6% increase between baseline and postintervention [53,55].

#### Self-Reported Exercise

Self-reported exercise will be assessed using the validated 3-item Godin Leisure-Time Exercise Questionnaire (GLTEQ) [56]. Using the GLTEQ, participants self-report how often in the previous 7 days they completed ≥15 minutes of strenuous, moderate, and light physical activity. The number of bouts at each intensity is then multiplied by the corresponding MET value and summed to create a Leisure Score Index (LSI). The proportion of participants considered sufficiently active will also be reported, determined based on prespecified LSI scores (<14 units=insufficiently active or sedentary; between 14 and 23 units=moderately active; and ≥24 units=active or “meeting criteria for being physically active”) [56,57].

#### Psychological mechanisms

Potential mediators of intervention effects will be assessed, including self-efficacy (Multidimensional Self-Efficacy for Exercise Scale [58]), habit strength (self-reported habit index [59]), motivation type (Behavioural Regulation Questionnaire [60]), and autonomy-supportive exercise environment (The Perceived Environmental Supportiveness Scale [61]).

### Data Analysis

#### Sample Size

We aim to recruit 40 participants over the course of 12 months. This sample size is considered sufficient to test the feasibility of delivering the intervention and other key trial parameters [62]. Notably, with this sample size, we will also have reasonable precision for estimating intervention adherence. For example, with a sample size of 40, if the average adherence rate observed in the study is 70%, we can be sure with 95% confidence that the true population proportion is between 56% and 85%; the 95% CI is ≥14.2. Given the potential reach of the intervention and the fact that adherence to current technology-based behavior change programs is 50% [39], this finding would warrant further investigation. The target sample size is also equivalent to approximately 20%-30% of the sample size needed to adequately power (80%) a future definitive trial to demonstrate noninferiority in VO_2_peak changes between groups (a *P* value of .05); based on differences observed in our formative work [19] and a systematic review [8].

#### Statistical Methods

The data will be presented descriptively where appropriate; this includes most feasibility outcomes (eg, recruitment rate, proportion of missing data, usability, and satisfaction), including the primary outcome (ie, adherence to the intervention), and safety outcomes (eg, number of adverse events, proportion of serious adverse events).

Changes in VO_2_peak, patient-reported outcomes (quality of life and fatigue), and physical activity behavior will be examined in exploratory analyses at all assessment time points using mixed model repeated measures analyses. Unadjusted and age- and treatment pathway–adjusted models will be conducted with standardized coefficients reported with 95% CIs to aid interpretation of clinical significance rather than *P* values given a lack of statistical power. The choice of modeling link will be informed by residual diagnostics. The data for withdrawn participants collected before study withdrawal will be retained for use in intention-to-treat analyses, unless requested otherwise by the participant.

Further exploratory analyses may include (1) examining changes in the proposed psychological mechanisms (eg, self-efficacy) from baseline to postintervention; (2) examining associations between the proposed mechanisms and the study outcomes (eg, adherence to exercise sessions and cardiorespiratory fitness); and (3) examining associations between participant characteristics (potential moderators) and intervention adherence (sessions and intensity), as well as changes in VO_2_peak. Given the small sample size and absence of a control group, a formal mediation analysis or moderation analysis will not be undertaken (as per Baron and Kenny [63]). However, the collection of these data will assist with determining the feasibility of mediator and moderator assessment in a larger trial, where a formal mediation analysis and moderator analysis may be undertaken.

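### The models are to report standardized coefficients for judging clinical significance, but every clinical threshold is in percent or raw units, and the ISWT is not named among the modelled outcomes

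*Protocol article*

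**What the plan says.** The Statistical Methods section lists what will be modelled: "Changes in VO_2_peak, patient-reported outcomes (quality of life and fatigue), and physical activity behavior will be examined in exploratory analyses", using mixed models for repeated measures. It then fixes the reporting scale and its purpose: "standardized coefficients reported with 95% CIs to aid interpretation of clinical significance rather than *P* values given a lack of statistical power". No other scale is named for the model results.

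The clinical criteria are set in the outcome sections:

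- VO2peak (Cardiovascular Fitness: VO2peak): the authors write "We expect an average improvement in VO_2_peak of ≥10" percent, and the same 10% is the threshold in the efficacy rule.
- ISWT (same section): "An improvement of ≥48 meters from baseline to postintervention will be considered clinically significant".
- FACT-B (Quality of Life): "A clinically important change in total quality of life has been defined as a 6% increase between baseline and postintervention".
- FACIT-Fatigue (Fatigue): "A clinically important change in the FACIT-Fatigue has been defined as a 6% increase between baseline and postintervention".
- Activity (Self-Reported Exercise): the proportion sufficiently active is "determined based on prespecified LSI scores", with cut points at 14 and 24 units.

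The efficacy rule covers the two fitness tests only. The programme is deemed potentially efficacious for fitness "if clinically significant changes in VO_2_peak (≥10%) or meters walked in the ISWT are achieved".

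**The concern.** The plan picks a reporting scale and states what it is for, and the scale does not suit that purpose. A standardized coefficient measures change in SDs of the sample. None of the protocol's thresholds is expressed that way, so a reader given only the coefficient and its interval cannot tell how the result stands relative to 10%, 48 m or 6%.

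The second part concerns the ISWT. The efficacy rule joins its two tests with an or, so the ISWT can support the claim by itself. According to the protocol, it was added because CPET might not be possible for every participant. It could therefore carry the decision when VO2peak is incomplete. Yet it is not named among the outcomes to be modelled.

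At stake is how readily the trial can apply its own prespecified efficacy criterion, and how useful the fitness estimates are for planning the later trial that the Introduction says they should inform.

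**Working it through.** The plan states no figure to reproduce on this point. The check sets the reporting scale beside each criterion and then sizes the gap under assumed spreads.

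**Step 1: scales side by side.**

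| Outcome | Unit of the criterion | Named in the modelled list? | In the efficacy rule? |
|---|---|---|---|
| VO2peak | percent change (10%) | yes | yes |
| ISWT | metres (48 m) | no | yes |
| FACT-B total | percent change (6%) | yes | no |
| FACIT-Fatigue | percent change (6%) | yes | no |
| Self-reported exercise | LSI units (14, 24) | yes | no |

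No criterion is in SD units. The LSI cut points classify a participant's activity level and are not thresholds for change, so the mismatch matters less there.

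**Step 2: what conversion needs.** For a linear model standardized by the outcome SD:

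- change in raw units = coefficient × SD
- percent change = coefficient × SD / baseline mean = coefficient × CV

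The ISWT needs the SD. VO2peak and the questionnaires need the SD and the baseline mean. The article gives none of these, so the spreads below are assumptions.

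**Step 3: thresholds expressed in SD units.**

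- VO2peak, 10% / CV: 0.10/0.15 = 0.67; 0.10/0.20 = 0.50; 0.10/0.25 = 0.40; 0.10/0.30 = 0.33.
- ISWT, 48 m / SD: 48/80 = 0.60; 48/100 = 0.48; 48/120 = 0.40; 48/150 = 0.32.
- Questionnaires, 6% / CV: 0.06/0.10 = 0.60, falling to 0.06/0.30 = 0.20.

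**Step 4: the reverse reading, for a reported coefficient of 0.5.**

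- VO2peak: 0.5 × 15% = 7.5%, up to 0.5 × 30% = 15%. The threshold is 10%.
- ISWT: 0.5 × 80 = 40 m, up to 0.5 × 150 = 75 m. The threshold is 48 m.

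In both cases the same coefficient can lie below or above the criterion, depending on the spread.

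**Step 5: the place of the ISWT.** Table 1 schedules it at baseline, post intervention and follow-up, as it does CPET, so the data suit the same repeated-measures model. The Statistical Methods section does not name it in the modelled list, nor among its examples of outcomes presented descriptively. The Results section says that the ISWT was added by amendment, which would fit a list that was not updated, although the article does not say so.

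**The case against.** The strongest reply is that nothing is lost. In an ordinary linear model the standardized coefficient is the raw one divided by an SD, and the analysts will have one observed SD, so multiplying back recovers the units. The ranges in the working reflect SDs unknown today, not an ambiguity that the analysts will face. This stands, and it limits the point to one of direct readability. A reader might infer that the coefficients can never be compared with the thresholds, or that the trial cannot produce the estimates it needs. Neither follows. Raw-unit results are not excluded, and the article condenses a fuller protocol. What remains is that the only scale the article commits to, for the express purpose of judging clinical significance, is not the scale of any criterion.

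A reader might also infer that the efficacy rule needs a confidence interval clear of its threshold, or that the decision would rest on unmodelled means in completers. The documents support neither. The rule asks only that clinically significant changes be achieved, the VO2peak expectation concerns an average, and data from withdrawn participants are kept for intention-to-treat analysis unless the participant asks otherwise.

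On the ISWT, the outcome section opens by saying that cardiovascular fitness, labelled VO2peak, is assessed by both tests, so VO2peak in the modelled list could be meant to cover both. It is therefore too strong to say that the ISWT is definitely excluded. But that reading is strained: the test is recorded in shuttles and judged in metres, no conversion to VO2peak is given, the cited correlation is moderate (r=0.61), and the efficacy rule treats the two as separate criteria.

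Finally, the models are labelled exploratory in a single-arm study of 40 with adherence as its primary outcome. That is correct and bears on severity.

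**Conclusion.** The point holds as a mismatch of scale and an incomplete list, not as an invalid analysis. The output named for judging clinical significance cannot be read directly against any of the protocol's thresholds without back-conversion. One of the two routes to the efficacy claim is not named among the modelled outcomes.

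Both parts rest on the text alone. The size depends on assumed spreads: with a baseline CV of 15% to 30%, the 10% VO2peak criterion corresponds to 0.67 to 0.33 SD; with an SD of 80 to 150 m, the 48 m criterion corresponds to 0.60 to 0.32 SD.

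The consequence is confined to the secondary efficacy criterion and the interpretation of the patient-reported outcomes. The primary adherence result, the safety criterion and the feasibility cut points do not depend on it. It should be corrected because the correction is cheap and the protocol sets out to be transparent about its prespecified criteria.

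**What to change.** In the Statistical Methods section:

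1. Make the main model output the mean change from baseline with its 95% CI, at post intervention and at follow-up, in the units of the criteria: percent for VO2peak, metres for the ISWT, points and percent for FACT-B and FACIT-Fatigue, and LSI units for activity. For VO2peak, a log-scale model or the mean change divided by the baseline mean would serve; the choice can be left to the analysts.
2. Name ISWT distance among the mixed-model outcomes.
3. Keep standardized coefficients as supplementary, stating which SD was used.

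The cost is one additional exploratory model and a few lines of wording. All the data are already scheduled in Table 1, and neither the sample size nor the primary analysis changes.
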